**Methods:**

The study is a 2-year nonrandomized controlled trial using 2 parallel groups. For the intervention group, we will combine palliative care treatment with a community promoter intervention, compared with a control group without intervention. Participants will be patients under a community palliative care team’s supervision with and without intervention. The community promotor will deliver the intervention in 7 sessions at 2 levels: the patient and family level will identify unmet needs, and the community level will activate resources to develop social networks to satisfy patient and family needs. A sample size of 320 patients per group per 100,000 inhabitants will offer adequate information and will give the study 80% power to detect a 20% increase in unmet needs, decrease families’ burden, improve families’ satisfaction, and decrease the use of health system resources, the primary end point. Results will be based on patients’ baseline and final analysis (after 7 weeks of the intervention). We will carry out descriptive analyses of variables related to patients’ needs and of people involved in the social network. We will analyze pre- and postintervention data for each group, including measures of central tendency, confidence intervals for the 95% average, contingency tables, and a linear regression. For continuous variables, we will use Student *t* test to compare independent samples with normal distribution and Mann-Whitney *U* test for nonnormal distributions. For discrete variables, we will use Mann-Whitney *U* test. For dichotomous variables we will use Pearson chi-square test. All tests will be carried out with a significance level alpha=.05.

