**Figure 1 figure1:**
[figure not shown]
Action procedures for the REDCUIDA protocol.

**Table 1 table1:** REDCUIDA protocol for applying assessments to the beneficiary and the networks of care.

Assessment	Evaluation step							
	V0	V1	V2	V3	V4	V5	V6	V7
Inclusion and referral sheet	Yes	—	—	—	—	—	—	—
Networks of care	Yes	Yes	Yes	Yes	Yes	Yes	Yes	—
Barthel Index	Yes	Yes	Yes	Yes	Yes	Yes	Yes	—
Lawton and Brody scale	Yes	Yes	Yes	Yes	Yes	Yes	Yes	—
Loneliness scale	Yes	—	—	—	—	—	Yes	—
Zarit Scale	Yes	—	—	—	—	—	Yes	—
EQ-5D-3L^a^	—	—	—	—	—	—	Yes	—
Family and network of care satisfaction	—	—	—	—	—	—	—	Yes

^a^EQ-5D-3L: 3-level EuroQol 5 dimensions questionnaire.

We have adapted Abel and colleagues’ circles of care (Multimedia Appendix 3) [6], which can be self-administered or assessed via a direct interview with the patient or their caregivers. We will detect social solitude using the expanded ESTE II Scale [32] adapted from De Jong Gierveld and Van Tilburg [33], which must be administered directly to the patient or by the caregiver (Multimedia Appendix 4). We will use the 3-level EuroQol 5 dimensions questionnaire (EQ-5D-3L) [34] to asses quality of life. This descriptive system contains 5 dimensions of health (mobility, personal care, daily activities, pain and discomfort, and anxiety and depression), and each has 3 levels of severity (no problems, some problems or moderate problems, and serious problems). This assessment is self-administered or completed directly by the patient (Multimedia Appendix 5). We will use the Zarit Scale [35,36] adapted into Spanish [37] to assess the variable burden of the caregiver in the provision of care to chronically ill patients, which is administered by directly interviewing the caregiver (Multimedia Appendix 6). The Satisfaction Scale, adapted from Villavicencio et al [38] and Molina et al [39] (Multimedia Appendix 7), will be conducted by an external professional by phone on completion of the interventions.

During the intervention processes and the creation of networks of care, the community promoter will follow a series of activities based on Horsfall and colleagues’ method for the creation of ecosystems of care around people at the end of life [40].

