At the end of the interventions, a final evaluation (V7) will be conducted to reevaluate the needs coverage by the network and to evaluate family and caregivers’ satisfaction. This phone questionnaire will be administered by an independent professional to avoid information bias.

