### Statistical Methods

We will carry out an initial descriptive analysis of variables related to patients’ needs and the profiles of people involved in the social network by degree of kinship.

We will analyze pre- and postintervention data for each group. These will include measures of central tendency (mean), confidence intervals for the 95% average, contingency tables (frequencies), and a linear regression.

To compare the groups, we will compare means. For continuous variables, we will use Student *t* test to compare independent samples with normal distribution and Mann-Whitney *U* test for nonnormal distributions. For discrete variables, we will use Mann-Whitney *U* test. For dichotomous variables (comparison of proportions), we will use Pearson chi-square test. All tests will be carried out with a significance level alpha=.05.

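### Family satisfaction is measured only at V7, so its planned pre/post analysis cannot be run and the nonrandomized comparison cannot be adjusted for baseline satisfaction

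*Protocol article*

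**What the plan says.** In the abstract (Methods), satisfaction is part of the sentence claiming 80% power. The listed aims include "decrease families’ burden, improve families’ satisfaction, and decrease the use of health system resources, the primary end point". The same paragraph says results will rest on baseline and final values at 7 weeks. The Hypothesis section expects family satisfaction to rise.

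Statistical Methods states: "We will analyze pre- and postintervention data for each group". It then plans a comparison of means between groups, by Student t test or Mann-Whitney U test for a score of this kind.

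The schedule is in the Intervention section. In Table 1 the row "Family and network of care satisfaction" has a single Yes, at V7, and dashes from V0 to V6. The text below the table says the scale "will be conducted by an external professional by phone on completion of the interventions". The closing paragraph agrees: "a final evaluation (V7) will be conducted to reevaluate the needs coverage by the network and to evaluate family and caregivers’ satisfaction". No section gives a satisfaction value before the intervention for either group.

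Under Recruitment Procedure, the intervention group is drawn from one named area and consists of those who accepted the promoter. The control group lives where no promoter is available.

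**The concern.** The analysis and the schedule do not fit together for this outcome. A pre/post analysis needs two values and the schedule yields one. An analysis plan written later cannot repair this, because the missing value would never have been collected.

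The gap would matter less in a randomized trial, where the groups start out alike on average and a post-only comparison is unbiased. Here allocation follows residence and, in the intervention area, acceptance of the promoter. If families in the two groups differ in satisfaction at the start, part of that difference may still be present at V7 and would be read as an effect. The Discussion treats satisfaction as one of the results that could justify new palliative care systems, so a false positive there would carry weight.

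**Working it through.** **Schedule against analysis (Table 1)**

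| Measure | Before the intervention | End |
|---|---|---|
| Loneliness scale | V0 | V6 |
| Zarit Scale | V0 | V6 |
| Family and network satisfaction | none | V7 |

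Loneliness and caregiver burden are taken twice, so paired measurement was feasible in this setting. For satisfaction, neither a change score nor a model with baseline satisfaction as covariate can be fitted.

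**The plan's own group size**

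The Sample Size Calculation section gives 320 per group. It reproduces as a count of available patients: 7000 per million × 100,000 = 700; 700 × 0.65 = 455; 455 × (1 − 0.30) = 318.5, close to 320. I use 320 below.

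**What a post-only comparison can detect**

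Smallest standardized difference at 80% power, two-sided alpha .05: (1.960 + 0.842) × √(2/320) = 0.22 SD. The comparison is not empty.

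**What an initial gap does to it**

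Assumptions, none of them given in the article: no true effect; an initial gap between groups of g SD; a fraction c of that gap still present at V7; complete data on 320 per group; a two-sided test (the article gives alpha = .05 without sidedness).

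The test statistic is shifted by s = c × g × √(320/2) = c × g × 12.65. The probability of a significant result is Φ(s − 1.96) + Φ(−s − 1.96).

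Example with g = 0.2 and c = 0.5: s = 0.10 × 12.65 = 1.265; Φ(−0.695) + Φ(−3.225) = 0.244.

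| Fraction c persisting | g = 0.1 SD | g = 0.2 SD | g = 0.3 SD |
|---|---|---|---|
| 0.3 | 6.7% | 11.8% | 20.7% |
| 0.5 | 9.7% | 24.4% | 47.5% |
| 0.7 | 14.4% | 42.5% | 75.7% |
| 1.0 | 24.4% | 71.6% | 96.7% |

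Every cell exceeds the nominal 5%. The bias itself is c × g and does not depend on the number of patients. In the example it is 0.10 SD, which is 0.10 / 0.22 = 45% of the smallest difference the comparison could detect. Loss of patients before V7 would lower the probabilities in the table but leave this bias unchanged.

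**The case against.** A reader might infer that improvement in satisfaction cannot be shown at all. The document does not support that. Statistical Methods also plans a between-group comparison, and a V7 comparison can show higher satisfaction than in controls. What is lost is change within groups and adjustment for baseline satisfaction.

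A reader might also infer that no baseline adjustment is possible. That is too broad. Table 1 has Zarit, loneliness, Barthel and Lawton at V0; the Variables section lists age, sex and diagnosis; and a linear regression is planned.

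Nor does the article say that local care differs between the areas. The Setting section calls the promoter their main difference, and the Limitations section concedes possible selection bias. An initial gap is therefore an assumption. Still, a main difference is not the only one, and conceding selection bias does not remove it.

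The strongest defence is the construct. The Variables section defines the outcome as satisfaction with the care network, which the intervention builds, so measuring it only afterwards may be deliberate. This stands for items about the new network. It does not stand for the comparison with controls, who get no promoter-built network. That comparison needs items about the support people have, and Table 1 already describes existing networks at V0. The items are in Multimedia Appendix 7, which is not shown, so whether they can be separated in this way is unknown.

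Finally, the pre/post sentence is general and may not have been meant for every variable. If so, the article should say that satisfaction is an exception, because the abstract and the hypothesis speak of improvement.

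**Conclusion.** The point holds in a limited form. Satisfaction is scheduled once, at V7; the stated pre/post analysis cannot be run for it; and the area-based comparison cannot be adjusted for baseline satisfaction. A V7 difference therefore cannot be told apart from a pre-existing one, although it can be detected.

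For an initial gap of 0.2 SD, the chance of a false positive is 11.8% to 42.5% when 0.3 to 0.7 of the gap persists, and 71.6% when all of it does. These figures illustrate the risk and do not estimate it: gap size and persistence are assumed, and the data are taken as complete.

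Two limits apply. The abstract's primary end point is singular and may mean resource use only, so satisfaction should not be called primary on this evidence. Table 1 describes the REDCUIDA protocol, and the article does not state when controls are asked about satisfaction.

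**What to change.** Preferred: at the baseline home appointment in both groups, before promoter contact, ask the family those satisfaction items that apply to the care and support they receive now. Repeat the same items at V7. Compare final scores adjusted for the baseline score and the other V0 measures. Keep items about the newly created network as a V7-only description.

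The cost is a few items and a slightly longer visit. Mode and assessor may differ from the final call, which is made by an independent professional to avoid information bias, while the baseline appointment is arranged by the palliative care team. Families might rate the team kindly in its presence. Self-completion out of the team's sight reduces this, and a baseline phone call would match the mode. Someone with access to Appendix 7 must first check which items make sense before a network exists. Adjustment removes only the measured part of an initial difference, so the selection caveat stays.

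If no baseline is added: state that satisfaction is a post-only between-group comparison; adjust it for Zarit, loneliness, Barthel, Lawton, age, sex and diagnosis, making sure these are collected in controls as well; and replace the wording about improvement with wording about a difference from control. This adds no new instrument, but baseline satisfaction remains uncontrolled.

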### Variables

The variables we will use for the descriptive study on the REDCUIDA protocol are the following: for patients’ clinical and sociodemographic data: age, sex, and diagnosis; for families’ sociodemographic data: age, sex, and relationship to the patient; for network of care profiles: relationship to the patient, age, and sex; number of needs according to Barthel Index and the Lawton and Brody scale; number of members of the care network; number of needs covered by the network; quality of life according to the quality of life scale EQ-5D-3L; degree of loneliness according to ESTE II Scale; burden of the principal caregiver according to the Zarit Scale; satisfaction regarding the care network according to the Satisfaction Scale; and place of death.

For community promoter activity data, we will determine the number of interventions performed at home and number of interventions carried out in the community (eg, district, neighborhood, city, community of neighbors).

To assess health care system resources, we will determine the number of hospital admissions in the last month; days of hospital stays in the last month; number of emergency visits in the last month; number of visits of the palliative care team to the home; number of visits of the palliative care team to a hospital; and number of telephone calls made by the palliative care team.

### Sample Size Calculation

We have calculated a sample size of 320 patients per group for a population of 100,000 inhabitants based on the number of people dying of cancer each year (7000 people per million inhabitants) and the number of people in the final stage of nononcologic illnesses (approximately 4500 cases per million inhabitant). In a population of about 700 people, per year, 65% will require specialized palliative care (455 patients eligible for the study [41]).

We have considered that 30% of patients will not sign the informed consent forms or will not meet all the inclusion and exclusion criteria.

### Sources of Information and Data Collection

We will collect data from the patient’s own medical history and the information from the REDCUIDA protocol.

Data regarding variables not included in the protocol, such as the use of the health care system, will be collected through a direct interview with the patient or caregiver and the principal health care professionals regarding visits in the last month (Multimedia Appendix 8). In addition, we will ask palliative care professionals for these data (before and at the end of the care process).

The community promoter and health care professionals will have access to the beneficiary’s clinical information once enrolled in a palliative care program. The permission of the beneficiary and their main caregiver or closest connection shall be required in writing and verbally in order to be able to access the data and use the corresponding data of the interventions for analytical purposes. To ensure confidentiality, the beneficiary’s identification data will be coded so that they can’t be identified by their clinical information.

The deidentified data will be returned to the community promoter and the New Health Foundation for data processing and analysis. The questionnaires will be coded with an alphanumeric identifier in a separate database independent of that containing the participant’s identification data.

### Statistical Methods

We will carry out an initial descriptive analysis of variables related to patients’ needs and the profiles of people involved in the social network by degree of kinship.

We will analyze pre- and postintervention data for each group. These will include measures of central tendency (mean), confidence intervals for the 95% average, contingency tables (frequencies), and a linear regression.

To compare the groups, we will compare means. For continuous variables, we will use Student *t* test to compare independent samples with normal distribution and Mann-Whitney *U* test for nonnormal distributions. For discrete variables, we will use Mann-Whitney *U* test. For dichotomous variables (comparison of proportions), we will use Pearson chi-square test. All tests will be carried out with a significance level alpha=.05.

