### Objective

The primary objective of this study is to evaluate the REDCUIDA intervention protocol for the creation and management of networks of care that cover the unmet needs of a person with advanced diseases or at the end of life.

The secondary objectives are to (1) identify the precise nature of a patient’s unmet needs by palliative care teams that can be addressed through mobilization of the community, (2) detect members of the support networks that can meet the patient’s identified needs and describe their fundamental characteristics (caregiver profiles), (3) analyze the influence of a community promoter’s interventions on the emergence and growth of support networks as the disease progresses, (4) assess whether the REDCUIDA intervention improves the patient’s quality of life and decreases the main caregiver’s burden, (5) establish whether this intervention reduces professionals’ workload and health and social resource consumption during end-of-life care, and (6) analyze the influence of the REDCUIDA intervention on the preference of the place of care and death.

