### Intervention

We will deliver the REDCUIDA intervention over the course of 7 weeks (Figure 1). Different interventions will take place each week during a face-to-face meeting between the community promoter and the person living with advanced illness, or their families, or both.

We will conduct an initial (V0) assessment of the sociodemographic data of the beneficiary and his or her needs. This first step aims to detect the degree of care and support networks that could be mobilized during the progression of the disease. At this point, the community promoter will complete the beneficiary’s referral sheet (Multimedia Appendix 1) and the requirements sheet (Multimedia Appendix 2 [29]). If more detailed information will be needed, a face-to-face meeting will be held with the health professional involved.

Following V0, we will determine the needs of care networks and interventions. Then, we will arrange a meeting among the beneficiary and his or her family, health care professionals, and the community promoter to inform all of them about creating and managing a specific caring network within their community (V1). This first visit will be used to understand the starting point as a baseline analysis for the activities ahead.

During the subsequent interventions, we will conduct several assessments (Table 1) based on the following scales. We will use the Barthel Index [29], in the original or a validated Spanish version [30], to identify needs related to basic daily living activities. This assessment can be self-administered, evaluated with direct observation, or completed by the patient or caregivers (Multimedia Appendix 2). We will use Lawton and Brody’s original scale [31] to identify needs for instrumental daily living activities. This assessment can be self-administered, directly observed, or completed by the patient or caregivers (Multimedia Appendix 2).

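### The stated pre/post analysis leaves the timing and shape of network growth (secondary objective 3) unaddressed, although Table 1 records the network at V0 to V6

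*Protocol article*

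**What the plan says.** - **Question.** The third secondary objective (Objective section) is to analyse the promoter's influence "on the emergence and growth of support networks as the disease progresses".
- **Data.** Table 1, titled "REDCUIDA protocol for applying assessments to the beneficiary and the networks of care", marks networks of care, Barthel, and Lawton and Brody at each of V0 to V6, with a dash at V7. The Intervention section sets the rhythm: "Different interventions will take place each week during a face-to-face meeting". The Variables section lists "number of members of the care network; number of needs covered by the network".
- **Analysis.** The abstract states: "Results will be based on patients’ baseline and final analysis (after 7 weeks of the intervention"). Statistical Methods states: "We will analyze pre- and postintervention data for each group". It then lists means, 95% confidence intervals, "contingency tables (frequencies), and a linear regression". Groups are compared by t test, Mann-Whitney U or Pearson chi-square. A separate initial descriptive analysis covers patients' needs and network members' profiles by kinship, and names no time points.
- **Baseline and final.** The Intervention section has an initial assessment at V0 but describes V1 as the baseline analysis. It says that V7 re-evaluates how far the network covers needs.

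**The concern.** Objective 3 is a question about a time course. Up to seven network records per patient are scheduled to answer it, and the analysis the article states uses two. A difference between two points cannot tell a network that forms in the first weeks from one that grows late. It also cannot relate weekly change in the network to weekly change in needs, although both are recorded on the same visits.

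Early death makes this matter more. The only prognostic exclusion is an expected survival under 1 week, while the intervention lasts 7 weeks, so some eligible patients may die before the final assessment. A baseline-to-final change cannot use the weekly records those patients did provide.

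**Working it through.** **Passages side by side.** Objective 3 asks about growth over time. Table 1 supplies V0 to V6. The abstract and Statistical Methods name baseline and final only. The named tests compare two independent samples, and the linear regression has no stated outcome or time term. If pre is V0 and post is V6, then V1 to V5 enter no stated analysis. If pre is V1, the visits left out are V0 and V2 to V5. If post is V7, Table 1 holds no network record at that point.

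**The plan's own figure.** The only sample-size figure is 320 per group, and it reproduces as a headcount: 100,000 × 7000/1,000,000 = 700; 700 × 0.65 = 455; 455 × 0.70 = 318.5. It carries no standard deviation, correlation or effect for network size. The abstract's 80% power statement concerns unmet needs, burden, satisfaction and resource use. Any gain from using all visits must therefore be shown over assumed values.

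**Assumptions.** Linear growth, complete data, seven equally spaced visits t = 0 to 6 (the V0-to-V1 interval is not stated), two-sided alpha 0.05, and a two-point analysis with 80% power.

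**Independent residuals.** Let s² be the residual variance and tau² the between-patient slope variance.

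- Seven visits: Σ(t − 3)² = 9 + 4 + 1 + 0 + 1 + 4 + 9 = 28, so v7 = tau² + s²/28.
- Two end visits: 2s²/6² = s²/18, so v2 = tau² + s²/18.
- Seven-visit power = Φ((1.960 + 0.842) × √(v2/v7) − 1.960).

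| tau² | v2/v7 | Seven-visit power | Gain (points) |
|---|---|---|---|
| 0 | 28/18 = 1.556 | 94% | 14 |
| s²/28 | 1.278 | 89% | 9 |
| s²/18 | 1.217 | 87% | 7 |
| s²/9 | 1.135 | 85% | 5 |
| s² | (1 + 1/18)/(1 + 1/28) = 1.019 | 81% | under 1 |

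**Serially correlated residuals.** Under AR(1), comparing the generalised least-squares slope over seven visits with the V0-to-V6 change, power rises from 80% to 82.1% at a weekly correlation of 0.5, to 80.4% at 0.7, and stays at 80.0% at 0.9 and 0.95. The gain is at most about 2 points.

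**Missing final visits.** No death or dropout rate is given. As an illustration, if a fraction f lacks the final visit, an analysis of complete pairs with 80% power at full data falls to Φ(2.802 × √(1 − f) − 1.960): 76% at f = 0.1, 65% at f = 0.3 and 51% at f = 0.5. A mixed model would regain only part of this, depending on how many visits those patients completed.

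**The case against.** The strongest reply has four parts.

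1. **This is a condensed article, and a repeated-measures model for one secondary objective is ordinary analysis-plan content.** That would settle the matter if the article were silent. It is not: it names its time points in two places, and they do not fit objective 3. The abstract's sentence follows the power and primary-endpoint statement and could be read as applying to that alone, but the sentence in Statistical Methods carries no such limit. What stands is that the full plan may use the intermediate visits, so one may say only that they enter no stated analysis.

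2. **A V0-to-V6 difference does describe growth.** This stands for net growth. A reader might infer that growth cannot be described at all, or that the intermediate data are discarded. The text supports neither: net change is estimable, and the initial descriptive analysis is not tied to two time points, though it covers needs and kinship profiles rather than growth.

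3. **No power is claimed for network size.** This stands. A reader might infer a clear loss of power. The table shows that such a loss needs nearly independent residuals and little variation in slope between patients. Large, stable differences in growth between patients, or serially correlated weekly counts, are both plausible and bring the gain close to zero.

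4. **Controls may have no weekly records.** This also stands. Table 1 is the schedule of the REDCUIDA protocol, tied to promoter meetings, and the control area has no promoter. Nothing says that controls are scored at V1 to V5, so baseline and final may be the only points common to both groups.

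**Conclusion.** The point holds as a mismatch between a stated objective, a stated schedule and a stated choice of time points. As written, objective 3 receives a net change and no trajectory, and patients who die before the final visit contribute no change. This does not depend on any power figure.

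The gain in precision is conditional: about 0 to 14 points above a two-point analysis with 80% power, under linear growth, equal spacing and complete data. The document gives no correlation or slope variance that would place the trial within that range, so the case for change rests on answering the question asked and on using incomplete records. The objective is secondary, and the point does not bear on the between-group comparison unless controls are scored on the same visits.

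A related inconsistency needs settling with it. The Intervention section places a needs-coverage re-evaluation at V7 where Table 1 shows no network assessment, and it calls V1 the baseline analysis although V0 is the initial assessment. Until these are reconciled, pre and post are not defined for the network outcomes.

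**What to change.** In the abstract's Methods and in Statistical Methods:

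- State that, for objective 3, the number of network members and the number of needs covered in the intervention group are analysed over all scheduled visits with a repeated-measures mixed model, using a count link where needed. Report both the trajectory and the last-visit estimate.
- State whether controls are scored at the intermediate visits. Add group-by-visit terms only if they are. Otherwise keep the between-group contrast at the common baseline and final points.
- Define the baseline and final visits for each outcome. Reconcile the V7 needs-coverage re-evaluation with Table 1, and V1 as baseline analysis with V0.

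**Cost.** Wording, and slightly more analysis work on data already scheduled, with no extra visits or patients for the intervention-group analysis. The price is a missing-at-random assumption for patients who die early, which should be stated beside the result.
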